#### Exclusion criteria

2.2.4

Major curve Cobb angle>40°, the patient has used brace.Non-specific scoliosis.Abnormalities in growth and development, as well as neurological, muscular, skeletal, and mental functions.The patient and guardian refuse or are unable to cooperate with the completion of the assessment.Participating in other relevant clinical studies.

#### Termination criteria

2.2.5

The termination criteria are as follows: (1) Participants’ voluntary withdrawal, such as revoking informed consent; (2) Participants whose condition progressively worsens during the trial, and for whom the physician determines discontinuation of the clinical trial is necessary. To protect the subject, they should withdraw from the trial; (3) During the trial, participants demonstrate poor compliance, fail to undergo intervention as specified; and (4) Participants are experiencing serious adverse events.

#### Sample size consideration

2.2.6

According to previous research (31), the Cobb angle was 10.87 ± 3.60°in EG after treatment, compared to 14.97 ± 5.01°in CG. Using the PASS 2021 software for calculation, with a sample size ratio set at 1:1, *α* = 0.05 (two-sided test), and a statistical power (1−*β*) of 0.90, while controlling the attrition rate within 15%, it is determined that 30 patients need to be recruited for each group. Therefore, this study will require the inclusion of a total of 60 patients. In addition, we will recruit 15 healthy individuals of the same age. They will compare with patients at baseline to evaluate biomechanical changes of AIS.

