#### Inclusion criteria

2.2.2

Diagnostic criteria for idiopathic scoliosis (1).Ages 8 to 15 years, skeletal immaturity (defined as a Risser grade ≤2) (29, 30).Major curve Cobb angle 10° ~ 40°.No obvious deformities in the lower limbs and feet.Can understand and follow instructions to walk independently.Can understand and voluntarily participate in, and sign the informed consent form.

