#### Data analysis

2.5.2

All statistical analysis will be performed by an independent statistician (blinded to group allocation) using SPSS 27.0. A *p*-value of <0.05 will be considered statistically significant. Continuous data will be summarized as mean ± standard deviation (M ± SD) or median with interquartile range. Categorical variables will be presented as frequencies or percentages.

This study will employ an intention-to-treat analysis, including all participants who were randomized and received at least one intervention session. Outcomes will be analyzed using two-sample *t*-tests or paired *t*-tests. If normality assumptions cannot be met, non-parametric tests will be used. For categorical variables, chi-square (χ^2^) tests will be performed. Inter-rater reliability will be assessed using the intraclass correlation coefficient. For case data with missing values, multiple imputation will be used to address the gaps.

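### The stated 90% power is not supported for 10°–40° curves if the between-group t-test is run on the raw post-treatment Cobb angle

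*Protocol article*

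**What the plan says.** Section 2.2.6 (Sample size consideration) takes its planning values from one earlier study: "the Cobb angle was 10.87 ± 3.60°in EG after treatment, compared to 14.97 ± 5.01°in CG". With 1:1 allocation, two-sided alpha of 0.05, power of 0.90 and "controlling the attrition rate within 15" percent, "it is determined that 30 patients need to be recruited for each group". The section gives no baseline angles and no entry range for that study, and does not say why its SDs should apply here.

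Section 2.2.2 (Inclusion criteria) admits "Major curve Cobb angle 10° ~ 40" degrees. Section 2.2.4 excludes curves above 40° and patients who have used a brace.

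Section 2.4.1 has the Cobb angle measured before and after treatment. Section 2.5.2 (Data analysis) states: "Outcomes will be analyzed using two-sample *t*-tests or paired *t*-tests". It names no baseline covariate and does not say whether the between-group test compares post-treatment angles or changes.

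**The concern.** The power calculation compares raw post-treatment angles, so its SD is the spread of curve size between patients. That spread depends on who is enrolled. The two planning distributions sit at the low end of the range that this trial admits, while eligibility is open up to 40°. If the enrolled curves are more widely spread than in the earlier study, the SD of the raw angle rises and power falls.

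This is the primary outcome of a 60-patient trial. If power were well below 90%, a non-significant result would be uninformative about a 4.1° benefit, yet the stated power would invite reading it as evidence of no added effect.

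**Working it through.** **Inputs from section 2.2.6:** post-treatment means 10.87° and 14.97°; SDs 3.60° and 5.01°; two-sided alpha 0.05; power 0.90; 1:1 allocation; attrition 15%; 30 per arm.

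**Input not in the documents:** the SD of the post-treatment Cobb angle in a 10°–40° population. It is varied below as an assumption.

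**1. Reproducing the plan's figure**
- Difference: 14.97 − 10.87 = 4.10°.
- Pooled SD: √((3.60² + 5.01²)/2) = 4.36°. Standardised difference: 4.10/4.362 = 0.94.
- Noncentral t with n per arm: df = 2n − 2, noncentrality = 4.10/(SD × √(2/n)). At n = 24 power is 0.890; at n = 25 it is 0.902. So 25 per arm are needed.
- Attrition: 25/0.85 = 29.4, rounded up to 30. The stated figure reproduces.

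**2. How far the planning distributions reach**
- Mean + 2 SD: 10.87 + 2 × 3.60 = 18.07° (experimental) and 14.97 + 2 × 5.01 = 24.99° (control).
- Under a normal approximation, about 2% of the control distribution lies above 25° and about 0.1% above 30°. The upper half of the eligible range is hardly represented.

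**3. Headroom**
- Largest SD that keeps 90% power for 4.10°: 4.38° with 25 completers per arm, 4.82° with all 30 analysed. The plan uses 4.36°.

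**4. Unadjusted power at assumed SDs (difference held at 4.10°)**

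| Assumed SD | Power, 25 per arm | Power, 30 per arm | Completers per arm for 90% |
|---|---|---|---|
| 4.36° (plan) | 90% | 95% | 25 |
| 5° | 81% | 88% | 33 |
| 6° | 66% | 74% | 46 |
| 7.07° | 52% | 60% | 64 |
| 8.66° | 37% | 44% | 95 |

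Two of these SDs have a simple reading. If curves were spread evenly over 10°–40°, the SD would be 30/√12 = 8.66°. If their frequency fell linearly from 10° to 40°, it would be 30/√18 = 7.07°.

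**5. What use of the baseline angle does**

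With correlation r between baseline and post-treatment angle, and equal SDs at both visits, the ANCOVA residual SD is SD × √(1 − r²). The SD of the change is SD × √(2(1 − r)). ANCOVA power with 25 per arm, r assumed:

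| SD | r = 0.7 | r = 0.8 | r = 0.9 |
|---|---|---|---|
| 6° | 91% | 98% | >99% |
| 7.07° | 80% | 92% | >99% |
| 8.66° | 63% | 78% | 96% |

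Worked entry: SD 7.07°, r = 0.8 gives 7.07 × √(1 − 0.64) = 4.24°, which is below the 4.38° limit, and power of 92%. A t-test on change at SD 8.66° has 74% power at r = 0.8 and 96% at r = 0.9.

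**The case against.** The calculation contains no error, and what remains is a dispute about a planning assumption. Several points on that side stand.

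- **A reader might infer that the SD here must exceed 4.36°.** The documents do not support that. Eligibility sets limits, not a distribution: a sample spread evenly over 10°–25° is fully eligible and has an SD of 15/√12 = 4.33°. Excluding patients who have used a brace may also thin out the larger curves.
- **A reader might infer that the earlier study enrolled only mild curves, or that its 4.10° gap reflects a baseline difference.** Its entry range and baseline angles are not given, and post-treatment angles are not entry angles. Neither inference can be checked.
- **A reader might infer that the planned test lacks 90% power.** Section 2.5.2 leaves open whether post-treatment angles or changes are compared. A test on change could reach 90% if the pre–post correlation is high, and a separate analysis plan may specify baseline adjustment.
- **A reader might infer that the trial would probably miss a true 4.1° benefit.** In the range shown, power with 25 completers falls below 50% at the widest SD, 8.66°, but not at the others. The difference was also held at 4.10°; it could differ in larger curves.

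These points limit the claim but do not remove it. Section 2.2.6 uses neither a change SD nor a correlation, so 90% power is undocumented for an analysis of change too. And relying on recruits clustering at low angles is an assumption that the protocol neither states nor secures.

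**Conclusion.** The point holds in conditional form. The 90% power is unsupported for the eligible population if the between-group test uses the raw post-treatment angle, because the SD is carried over without justification and the margin after the planned attrition is about 0.02° (4.38° against 4.36°). The size of the shortfall is not known: over assumed SDs of 5° to 8.66°, power runs from 81% down to 37% with 25 per arm, and from 88% down to 44% with 30. These figures assume a true difference of 4.10°, equal SDs in the two arms and a two-sided test at 0.05. The documents do not establish that the trial is underpowered. Confidence is high that the justification is missing and moderate on the consequence, so this should be fixed but does not invalidate the design.

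**What to change.** Keep 60 patients and change two sections.

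- **Section 2.5.2:** name ANCOVA of the post-treatment Cobb angle, adjusted for the baseline Cobb angle, as the primary between-group analysis. The baseline angle is already collected.
- **Section 2.2.6:** either justify 4.36° for curves of 10° to 40°, or restate the power conditionally. Suggested sense: with 25 completers per arm, power is 90% for a 4.1° difference only if the SD of the analysed, baseline-adjusted quantity is at most about 4.4°. Keep recruited and analysed numbers apart in that sentence, since the limit is 4.82° if all 30 are analysed. Add a short power table over SD 5° to 8.7° and r 0.7 to 0.9.

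The cost is rewording and one small table, with no extra patients or measurements. The stated power becomes conditional and may look less favourable: at SD 8.66° and r = 0.8, even the adjusted analysis has 78% with 25 per arm.

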#### Randomization and blinding

2.2.7

Eligible patients will be randomly assigned to either the EG or the CG in a 1:1 ratio. The randomization sequence will be generated by a statistician not involved in outcome assessment using SPSS 27.0, and placed in opaque, sealed envelopes by a researcher not involved in trial intervention, assessment and data analysis. After an eligible patient is enrolled, the physician will obtain the allocation result by opening the corresponding envelope. Throughout the trial, the randomization sequence will remain inaccessible to other researchers. While blinding of the physicians and patients is not feasible, outcome assessors and the data statistician will remain blinded to group allocation.

### Interventions

2.3

Patients in both groups will receive the Schroth method for 60 min, 5 times per week. In addition to the Schroth method, the EG will receive TCMMT for 20 min, 3 times per week. The total treatment duration for both groups will be 8 weeks. The HC will receive no treatment.

#### The Schroth method

2.3.1

The Schroth method will include daily postural training (sitting, lying, and standing), personalized breathing exercises, simplified three-dimensional correction, and strengthening exercises (32). Specific operational procedures are detailed in Table 1.

**Table 1 tab1:** Specific operational procedures of the Schroth method.

Operation item	Specific operational procedures
Daily postural training (sitting, lying, and standing)	The patients will be instructed to shift their body weight toward the concave side, abduct the arm on the concave side slightly above shoulder level, rest the elbow on a horizontal bar, and place the hand behind the head. During the side-lying position, the patients should lie on the concave side of the curvature, allowing the spinal convexity to shift toward the midline under the influence of gravity.
Personalized breathing exercises	The patients will be instructed to straighten their torso and perform deep breathing. The practitioner will apply gentle pressure with the palm of the hand on the concave side of the spinal curvature. The patients will be asked to take a deep, diaphragmatic breath, and during inhalation, to slowly expand the area under the practitioner’s hand, pushing against the pressure.
Simplified three-dimensional correction	Including core components such as midline shift, pelvic adjustment, rotational breathing, and muscular contraction force generation. Corrective movements will be integrated into daily postures and activities.
Strengthening exercises	The patients will sit facing the wall bars with the concave side of the spine oriented toward them. To stabilize the trunk, the thighs will be abducted and externally rotated. The hand on the convex side will be placed on the ipsilateral shoulder to perform shoulder counter-traction. The hand on the concave side will be passed through a horizontal bar at shoulder height and will grip a bar at waist level, thereby opening the thoracic concave side.

#### Traditional Chinese Medicine manual therapy

2.3.2

The proprietary spinal balance-regulating TCMMT developed by the Rehabilitation Department will be applied to soft tissue relaxation and joint adjustment. First, the dynamic balance of the spine will require adjustment, including relaxing the bilateral paraspinal muscles, releasing the persistently contracted muscles on the concave side and the tense muscles on the convex side. Following this, Chiropractic spinal manipulations will be performed at the spinal levels that do not maintain correct alignment, including the cervical, thoracic, lumbar vertebrae, or pelvis. The specific operational methods and durations are detailed in Table 2.

**Table 2 tab2:** Specific operational procedures of the Traditional Chinese Medicine manual therapy.

Operation item	Specific operational procedures
Regulating the dynamic balance of the spine	
Relaxing the bilateral paraspinal muscles	The practitioner will apply the palm of the hand to the spine and the bilateral paravertebral muscles, and move in a unidirectional straight or arc-shaped line parallel to the spinal column to relax the paravertebral muscles, with each session lasting 4 min. The practitioner will hold the four fingers together with slight flexion and naturally abduct the thumb slightly. Using the dorsal metacarpophalangeal joints of the little, ring, and middle fingers to contact the paraspinal muscles, the practitioner will perform the manual therapy through a continuous external rotation movement of the wrist joint, with each session lasting 4 min.
Releasing the persistently contracted muscles on the concave side	The practitioner will use the thenar eminence or the heel of the palm to apply focused pressure on the paraspinal muscles of the convex side. A rotary movement will be performed using the wrist joint, with moderate, even force and a steady rhythm. Each session will last 5 min.
Releasing the tense muscles on the convex side	The practitioner will use the thumb(s) of one or both hands to apply deep pressure to the paraspinal muscles. Once a sensation of soreness or pain is perceived under the finger(s), a back-and-forth plucking motion, similar to plucking a string, will be performed. Each session will last 5 min.
Chiropractic spinal manipulations: Adjust the static balance of the spine at the spinal levels that does not maintain correct alignment, include the cervical, thoracic, lumbar vertebrae or pelvis. Each session will last 2 min.	
Cervical spine adjustment	The patient will lie in a supine position. The practitioner, positioned at the head of the patient, will firmly grasp the posterior aspect of the patient’s cervical spine. A manual adjustment will be performed while maintaining traction.
Thoracic spine adjustment	The patient will lie in a prone position. Taking a right thoracic curve as an example, the patient’s head will be tilted toward the convex side. The practitioner will apply pressure with the palm along the thoracic spine. Using the thumb, the spinous processes of the thoracic vertebrae will be sequentially pushed, focusing particularly on the apical vertebra of the curve.
Lumbar spine adjustment	The patient will lie in a lateral decubitus position. Hip and knee flexion will be used to position the axis of spinal rotation at the L3-L4 level. The practitioner will apply pressure with the thumb against the lumbar spinous processes and perform adjustments sequentially.
Pelvic adjustment	For anterior or posterior pelvic tilt, the practitioner will brace against one ischial tuberosity and the superior aspect of the contralateral ilium, applying an impulse in opposite directions.

### Outcomes measures

2.4

Collect general information of participants, including name, gender distribution, age, risser grade distribution, height, weight, and medical history.

#### Primary outcome measure

2.4.1

All AIS patients will require the standing frontal radiograph. The Cobb angles will be measured by two blinded and independent radiologists before and after the treatment.

#### Secondary outcome measures

2.4.2

All participants will be assessed for plantar pressure, 3D gait parameters, sEMG and muscle temperature at baseline upon enrollment. AIS patients will receive a second assessment after completing the treatment. All participants will acclimatize to the testing environment for 10 min before data collection. The indoor conditions will be maintained as follows: a quiet setting with minimal air movement, absence of strong light or direct sunlight, an ambient temperature of 26 °C, and a relative humidity of 40–60%. Air conditioning vents or outlets will be positioned away from both the participants and the equipment to prevent direct airflow or radiant heat from interfering with the participants or the infrared thermal camera.

##### Plantar pressure and 3D gait parameters

2.4.2.1

Plantar pressure measurement and 3D gait analysis provide critical information on kinematic, kinetic, and spatiotemporal parameters (33, 34). The data extracted from these analyses can be used for gait abnormality analysis, sports performance evaluation, balance control improvement, and the detection of functional impairments, among other applications (35, 36).

In this study, the biomechanics of plantar pressure distribution and standing balance status will be evaluated by using the FeetMapping plate-type plantar pressure measurement system. This system will be used in conjunction with the RealGait 3D gait and motion analysis system to collect spatiotemporal gait parameters and joint range of motion during walking.

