##### Surface electromyography

2.4.2.2

The activities of the bilateral paraspinal muscles (at cervical, thoracic, and lumbar levels), quadriceps, semitendinosus, tibialis anterior, and lateral gastrocnemius will be measured by a 16-channel MyoMove-EOW sEMG system to systematically evaluate the overall muscle activation patterns of the spine and lower limbs during standing and walking states. Recordings will be obtained during both quiet standing and walking. Muscle recruitment will be assessed by analyzing the amplitude variation of the bioelectrical signals, with the root mean square value recorded for quantitative analysis.

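### Gait measures that depend on body size are compared between arms by unadjusted tests in children aged 8 to 15, although height and weight are recorded; this can cost precision on secondary outcomes but causes no bias.

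*Protocol article*

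**What the plan says.** All places are in the protocol article.

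- **Population.** Section 2.2.2 admits patients at "Ages 8 to 15 years", restricted to Risser grade 2 or below.
- **Body size.** The general information in section 2.4 includes "risser grade distribution, height, weight, and medical history".
- **Gait and plantar measures.** Section 2.4.2.1 uses the gait system "to collect spatiotemporal gait parameters and joint range of motion during walking". Walking speed and step length are not named. The plantar plate is used for pressure distribution and standing balance; no absolute load measure is named.
- **sEMG.** Section 2.4.2.2 records standing and walking, "with the root mean square value recorded for quantitative analysis", and reads the amplitude as muscle recruitment.
- **Analysis.** Section 2.5.2: "Outcomes will be analyzed using two-sample" or paired t-tests, with non-parametric tests if normality fails. It names no covariate, and does not say whether post-treatment values or changes are compared between arms.

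**The concern.** Between 8 and 15 years children differ widely in height and weight. Step length, stride length and walking speed depend on height, and absolute plantar load depends on weight. A two-sample test on post-treatment values leaves all of that variation in the error term, although the variables needed to remove it are already on the case report form. This is a stated method applied to all outcomes, not merely a detail left out of the article.

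The trial is sized for a large effect on the Cobb angle only, so the gait and plantar outcomes have no planned power of their own. The Discussion and Conclusion nevertheless intend to draw conclusions on gait and overall biomechanics. A modest real effect on a size-dependent measure could be missed for an avoidable reason.

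**Working it through.** **1. The plan's own figure.** Section 2.2.6 gives the basis: "the Cobb angle was 10.87 ± 3.60°in EG after treatment, compared to 14.97 ± 5.01°in CG", two-sided alpha 0.05, power 0.90, equal allocation, attrition 15%.

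- Difference = 14.97 − 10.87 = 4.10.
- Pooled SD = √((3.60² + 5.01²)/2) = 4.36, so the standardised effect is 4.10/4.36 = 0.94.
- Noncentral t: 25 per arm (power 0.902). 25/0.85 = 29.4, rounded up to 30.

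The stated 30 per group is reproduced, and this point does not affect it.

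**2. Share of variance due to body size (step length as the example).** Assumptions, none of them in the documents: step length proportional to height; coefficient of variation of height (CVh) 7% to 10%; remaining coefficient of variation of step length (CVr) 6% to 10%.

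Share = CVh²/(CVh² + CVr²). Equivalent gain in sample size = 1 + (CVh/CVr)².

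| CVh | CVr | Share | Gain |
|---|---|---|---|
| 0.07 | 0.10 | 0.0049/0.0149 = 0.33 | 1.49 |
| 0.10 | 0.10 | 0.0100/0.0200 = 0.50 | 2.00 |
| 0.07 | 0.06 | 0.0049/0.0085 = 0.58 | 2.36 |
| 0.10 | 0.06 | 0.0100/0.0136 = 0.74 | 3.78 |

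**3. What this means at 30 per arm.** Let R² be the assumed share of outcome variance explained by body size. Removing it multiplies the residual SD by √(1 − R²). Effects are in units of the unadjusted SD; the small loss of degrees of freedom from covariates is ignored.

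| R² | Effect detectable with 80% power | Power for a 0.5 SD effect |
|---|---|---|
| 0 (as planned) | 0.74 | 48% |
| 0.1 | 0.70 | 52% |
| 0.3 | 0.62 | 62% |
| 0.5 | 0.52 | 77% |
| 0.7 | 0.40 | 94% |

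With 25 per arm after attrition, the detectable effect is 0.81 unadjusted and 0.77 to 0.44 for R² of 0.1 to 0.7.

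**4. When the loss shrinks.** If within-patient values correlate at r over the 8 weeks and the variance is stable, a change score has variance 2(1 − r) times that of a post-treatment value: 1.0 at r = 0.5, 0.6 at r = 0.7, 0.2 at r = 0.9. A body-size contribution that is stable over 8 weeks is common to both visits and subtracts out. The table in step 3 therefore applies to post-treatment values only.

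**5. Walking speed and sEMG.** Suppose mean speed differs between arms by 0.3 to 0.8 SD, speed correlates with RMS amplitude at 0.3 to 0.7 (all assumed), and recruitment at a given speed is the same. An unadjusted test at 30 v 30 is then significant in 6% (0.3 SD, 0.3), 16% (0.5 SD, 0.5) or 57% (0.8 SD, 0.7) of trials. These figures presuppose a true speed gap. Under randomisation a systematic gap can arise only through the treatment, so they do not show that the test of no treatment effect exceeds 5%. They show why amplitude should not be read directly as recruitment.

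**The case against.** The strongest reply is that a condensed article commonly leaves scaling, gait processing and walking conditions to the full protocol, the analysis plan or operating procedures, and section 2.6 promises standardised procedures. That stands: silence on walking speed or sEMG processing is no finding. The point rests only on the tests that section 2.5.2 names.

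It is also fair that section 2.5.2 allows paired tests and leaves open whether changes are compared. The sample size is built on post-treatment means, which suggests post-treatment values but does not settle it. The loss is therefore conditional.

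Three stronger readings are tempting and are not supported:

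- **Body size biases the comparison between arms.** It does not. Allocation is random, so size is balanced in expectation and only precision suffers.
- **Speed is collected, and a difference that vanishes after speed adjustment is not recruitment.** Speed is only inferred from the reference to spatiotemporal parameters. Speed at the post-treatment visit is also a post-randomisation variable: if treatment changes recruitment and patients then walk faster, such a rule would suppress a real effect.
- **All gait, plantar and sEMG outcomes are affected.** Joint range of motion is an angle, the plantar measures named are distribution and balance, and standing sEMG does not involve walking speed.

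The range of 1.5 to 3.8 also concerns one measure that the article never names, under exact proportionality. The Risser limit may narrow the height spread among older patients.

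**Conclusion.** The point holds as an inexpensive improvement to secondary analyses. For size-dependent gait measures, and for any absolute plantar load measure, the stated unadjusted tests give away precision if post-treatment values are compared between arms. The size cannot be fixed from the documents: 33% to 74% of step-length variance under the assumed coefficients of variation, and a detectable effect at 30 per arm that falls from 0.74 SD to between 0.70 and 0.40 SD for assumed R² of 0.1 to 0.7. In paired or change-score analyses most of this disappears. The primary Cobb angle analysis and the sample size are untouched. On walking sEMG, the documents support a caution in interpretation and nothing more.

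**What to change.** Add to section 2.5.2:

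> Size-dependent gait measures are scaled to height, and any absolute plantar load measures to body weight, before group comparison, or baseline height and weight enter as covariates in a linear model.

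Choose one of the two options before outcome data are seen, and state whether post-treatment values or changes are compared.

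If walking speed is extracted, speed-adjusted walking sEMG amplitude may be shown as a sensitivity analysis beside the unadjusted comparison between arms. Add a caution that amplitude is not a direct reading of recruitment and that post-treatment speed may itself respond to treatment. Set no rule that bars reporting a difference.

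The cost is wording. Height and weight are already recorded, no patient or visit is added, and two covariates use two of the 58 residual degrees of freedom at 30 per arm. The optional speed analysis requires speed to be among the extracted gait parameters, which the article does not confirm.
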